### **6 Transcranial Pulsed Current Stimulation (tPCS)**

- Real-tPCS for the intervention group - 20min/ session of tPCS will be performed at the participating site by a trained therapist or doctor, Monday to Friday for 20 sessions over 4 weeks in the study period.
- Sham-tPCS for the control group – everything the same as active-tPCS, except there is current output for only the first 10s of stimulation and the output will automatically zeroizes for the remaining time of the 20-min session.

- The same therapist/ doctor will not take part in patient assessments.
- Parents / caregivers of both groups will be asked to fill out the adverse event log after each session.

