### **2.4 Potential Risks and Benefits**

#### **2.4.1 Potential Risks**

tPCS may cause discomfort or tingling sensation to some people. Some people may have skin redness due to allergic reaction to electrode. Few people may complain of headache post stimulation. Otherwise, there is minimal risk in tPCS if there are no contraindication.

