### 3.7 Drop-out Criteria

- A. Subjects that withdrew midway due to adverse events
- B. Subjects where treatment was interrupted for more than 7 days during the study, due to sickness such as acute respiratory tract infection.
- C. Subjects who failed to complete the course of treatment due to poor compliance or unexpected changes in parents' demands.
- D. Subjects whose circumstances no longer adhere to the inclusion and exclusion criteria midway through the trial, Eg. non-compliance of treatment protocol, subjects who begin a drug or treatment course in the exclusion criteria, without informing the study team.
- E. Cases where significant human errors were involved including administration of incorrect treatment dose and not being assessed according to the evaluation standards set in this trial during the pre- and post-treatment assessments.
- F. Subjects with significant missing items in the pre- and post-evaluations resulting in incomplete data.

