## 4.3 Study Visits and Procedures

| Visit to Site                                                                                                                                | Visit 1             | Visit 2-21          | Visit 22                  |
|----------------------------------------------------------------------------------------------------------------------------------------------|---------------------|---------------------|---------------------------|
| Timeline                                                                                                                                     | Week 0              | Week 1-4            | Week 4                    |
| Procedure                                                                                                                                    | Baseline assessment | Intervention Period | Post-treatment assessment |
| Informed Consent                                                                                                                 | X                   |                     |                           |
| ATEC 2 ,                                                                                                                          | X                   |                     | X                         |
| ABC  ,                                                                                                                           | X                   |                     | X                         |
| CSHQ 4 ,                                                                                                                          | X                   |                     | X                         |
| WISC 5                                                                                                                            | X                   |                     |                           |
| Urine test                                                                                                                                   | X                   |                     | X                         |
| Real-tPCS 6 + 1 Hour Standard Therapy 7

or

Sham-tPCS 6 + 1 Hour Standard Therapy 7 |                     | X                   |                           |

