### **4.4 Discontinuation**

Study intervention will be discontinued if subject is unable to tolerate the tPCS or standard behavioral therapy as well as if drop-out criteria is met as per Section 3.7. Subjects may withdraw voluntarily from participation in the study at any time due to any reason. If withdrawal occurs, subjects will be asked to complete a form to state the reason for withdrawal.

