#### 6.2.4 One day (approximately 3 hours) of post-treatment assessment of ATEC, ABC and CSHQ, performed by qualified occupational therapists and child psychologists, through clinical observation and parent interviews.

### 6.3 Specific treatment adherence requirements/strategies

In this study, the tPCS intervention will be provided to participants free-of-charge in the eight hospital sites. The participants will not receive any monetary payments or gifts for their participation in the study.

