## 7.4 Complaint Handling

If there is any complaint of the tPCS, the Principal Investigator and Co-Investigators will be informed immediately to rectify the issue. If the subject is unable to tolerate the tPCS, the study will be discontinued for the subject.

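### The only scheduled adverse event enquiry is the log after each tPCS session, so new events after sessions end rely on unsolicited reports

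*Combined protocol and SAP*

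**What the plan says.** **Routine collection.** Section 4.3, footnote 6: "Parents / caregivers of both groups will be asked to fill out the adverse event log after each session". Sessions run "Monday to Friday for 20 sessions over 4 weeks in the study period", so a completer's family has 20 scheduled occasions to report. The log's recall period is not stated, and the log is not among the data forms in Appendices 1 to 3 (ATEC, ABC, CSHQ).

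**Last visit.** In the Section 4.3 table, Visit 22 (Week 4, "Post-treatment assessment") carries ATEC, ABC, CSHQ and a urine test. There is no adverse event row and no later visit. Section 6.2.4 describes the visit as "One day (approximately 3 hours) of post-treatment assessment of ATEC, ABC and CSHQ".

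**Stopping early.** Section 7.4: "If the subject is unable to tolerate the tPCS, the study will be discontinued for the subject". Section 4.4 also ends the intervention when a Section 3.7 criterion is met. Those criteria include withdrawal for an adverse event, an interruption of more than 7 days, and "Cases where significant human errors were involved including administration of incorrect treatment dose". Afterwards, Section 3.8 has the researcher ask why the child left and note the last session, with post-treatment assessment on a best-effort basis. Section 4.4 adds "If withdrawal occurs, subjects will be asked to complete a form to state the reason for withdrawal".

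**Other routes.** Section 7.3 has all adverse events of tPCS in all participants logged and monitored by the investigators. Section 7.2 keeps a site-file record of related events; its active follow-up is in the text on reporting related serious events. Section 7.4 sends complaints to the investigators at once. Section 9.2.3 adds monitoring of discomfort and a urine test before and after the intervention.

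**Analysis.** Section 9.2.3 reports adverse events in the full study population and provides a chi-square test for comparing incidence between arms.

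**The concern.** The scheduled enquiry follows the sessions, not the child. When sessions end, on plan or early, nobody is due to ask about adverse events again, although tolerance is one of the things that ends sessions. A chi-square test on incidence treats a child asked 5 times and a child asked 20 times as equally observed.

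The documents name a risk that need not appear while the child is on site: "Few people may complain of headache post stimulation" (Section 2.4.1). Section 1.2.3 also cites mania and hypomania, though from adult tDCS trials in depression. Section 9.2.3, by contrast, treats potential side effects as confined to the skin under the electrodes.

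At stake are the completeness of the adverse event table and the fairness of the arm comparison. For non-serious events that led to stopping, the plan also gives no set way to learn whether they resolved.

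**Working it through.** The plan gives no figure for adverse event coverage, so there is none to reproduce. The check sets the sections side by side, then bounds the number of children affected.

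**1. Who is asked, and when**

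| Situation | Scheduled adverse event enquiry | Other routes |
|---|---|---|
| Attending sessions 1-20 | Parent log after each session (4.3, footnote 6) | Investigator logging (7.2, 7.3), complaints (7.4), discomfort monitoring (9.2.3) |
| Session 20 to Visit 22 | None | Urine test; about 3 hours on site with parent interviews, where an event could be volunteered |
| After Visit 22 | None; no contact planned | Unsolicited reports; active follow-up stated only in the related serious event text (7.2) |
| After stopping early | None; reason and last session only (3.8, 4.4) | Best-effort post-treatment assessment with no adverse event item named; 7.2 and 7.3 as above |

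The other routes give no schedule, window or method of asking. Section 7.3 is also worded for events of tPCS, whereas Section 7.1 defines an adverse event regardless of relatedness.

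**2. What this does to an incidence comparison**

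Let p be the true four-week incidence in an arm, and m the share of its cases missed because their first event fell after sessions ended and was not volunteered.

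- Recorded incidence = p(1 - m).
- Recorded ratio, active to sham = (p_A / p_S) x (1 - m_A) / (1 - m_S).
- If m_A = m_S = m, the ratio is unchanged and the difference shrinks to (1 - m)(p_A - p_S): under-counting and lower precision, with no change of direction.
- If m_A > m_S, the active arm's incidence is understated relative to sham; if m_A < m_S, the reverse.

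A child who stops because of an event that was logged or given as the reason is already a case and adds nothing to m for that event. What can be lost is a first event in a child who stopped for another reason, a later event of a different type, and the duration or outcome of the event that led to stopping. The documents give no value for m in either arm.

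**3. How many children**

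Inputs: 340 children, 170 per arm (Section 4.2); dropout of 30%-40% (Protocol Deviations), with 40% used in Section 9.1.

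- 0.30 x 340 = 102; 0.40 x 340 = 136.
- Per arm, if equal: 0.30 x 170 = 51; 0.40 x 170 = 68.

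These are upper bounds on early stops at those dropout rates. Section 3.7 E and F also count as dropouts children with faulty assessments or missing questionnaire items, and such children can complete all 20 sessions. For scale, a child who stops after 5 sessions (an assumed value) has 5/20 = 25% of a completer's scheduled occasions to report.

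**The case against.** The strongest reply is that the log does not stand alone. Section 7.3 covers all participants, Section 7.2 keeps a record of related events, and withdrawal for an adverse event is a named category (3.7 A) that enters an analysis (9.2.2). Procedures are the same in both arms, and the dropout allowance is attributed to travel restrictions, not intolerance. All of this stands. It limits the point to what is asked on schedule, and makes bias between arms conditional.

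Some stronger readings are tempting but unsupported:

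- *Events outside the log are never recorded.* Sections 7.2, 7.3 and 9.2.3 provide other routes, and the reason for withdrawal can identify the event that led to it.
- *Safety coverage after session 20 is nil.* Visit 22 is in person and includes a urine test, and Section 7.1 counts abnormal laboratory findings as adverse events. What is missing is the question.
- *Harm in the active arm is understated.* This needs earlier stopping or more unreported late events in that arm. The documents show neither.
- *A fifth of the safety data is lost.* If all 136 dropouts stopped after 10 sessions on average, 136 x 10 / (340 x 20) = 20% of log entries would be absent (10% or 30% if after 15 or 5). That counts entries, not children, and treats every dropout as an early stop.
- *The log covers only time on site.* Its recall period is undefined, and a log completed after one session could carry events since the last.

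It is also fair to say that asking at Visit 22 adds little time for completers, since session 20 and Visit 22 both fall in Week 4. The larger gain is for children who stop early.

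**Conclusion.** The point holds as a gap in scheduled collection. Followed as written, the plan stops asking about adverse events when sessions stop, then compares incidence across all children as if they had been observed equally. Under-counting of late events is the expected consequence. Bias between arms follows only if early stopping, or unreported late events, differ by arm. At most 102-136 of 340 children would leave scheduled enquiry early at the plan's own dropout rates, and fewer in practice. The size of any under-count cannot be estimated from the documents.

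This rests on the text available: the log form is not shown and some pages, including the consent forms, could not be checked. The ATEC comparison is not affected. It is a worthwhile, low-cost improvement to data collection, not a flaw that undermines the trial.

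**What to change.** 1. In Section 4.3, footnote 6, define the log as covering all events since the previous entry, including evenings and weekends. No second log at each session is then needed.
2. Add an adverse event row at Visit 22 in the Section 4.3 table, with matching wording in Section 6.2.4.
3. For every child who stops early, complete the same log at the contact already provided for in Section 3.8, and again by phone on the child's planned week-4 date.
4. Record the outcome of any event still open at the last contact.
5. In Section 9.2.3, base the arm comparison on the common four-week window for all randomised children.

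**Cost.** Protocol wording, one table row, a little form time, at most one additional week-4 call per early stopper (no more than 102-136 calls at 30%-40% dropout), and occasional calls about open events. No visit or procedure is added. Reported event counts will probably rise. New events that start after Week 4 would still rely on unsolicited reports, and the protocol should say so.

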## **7 Standard Behavioural Therapy**

Standard therapy comprises of 1-hour of one of the following therapy programs - Applied Behaviour Analysis (ABA), structured learning, play-based therapy and speech therapy. Standard therapy is performed by experienced therapists with at least five-year experience.

### **4.4 Discontinuation**

Study intervention will be discontinued if subject is unable to tolerate the tPCS or standard behavioral therapy as well as if drop-out criteria is met as per Section 3.7. Subjects may withdraw voluntarily from participation in the study at any time due to any reason. If withdrawal occurs, subjects will be asked to complete a form to state the reason for withdrawal.

## **5 Trial Material**

### **5.1 Trial Product**

The tPCS device that will be used is the Multi-channel Pulsed current stimulator, model YQ-D1111, manufactured by YIQI Biotechnology Co. Ltd in China. The device has 11-channels, set at maximum current amplitude of 2mA. Each participant will only use one channel for scalp stimulation. The device can accommodate up to maximum 11 participants at a time in hospital setting. Both the active-tPCS and sham-tPCS devices will be this same model and look identical. The sham device will output current only for the first 10 seconds, then zeroized for the remainder session but the light on screen will remain throughout the treatment session to give the impression that stimulation is ongoing.

### **5.2 Trial Device Characteristics ):**

- Range of Current Amplitude (all 11 channels): 0.00 mA – max 2mA
- Waveform: Unilateral monophasic square wave
- Frequency: 400Hz
- Pulse width: 140µs

### 5.3 Electrode materials

Circular silver-fiber cotton electrodes, 4cm-diameter, 12.56cm^2 surface area. Secure to scalp using Velcro head strap (See Figure 2 below)

**Figure 2. 4cm-diameter, 12.56cm^2 circular silver-fiber cotton electrode and black Velcro head strap**

## 6 Treatment

### 6.1 Rationale for Selection of Dose

Based on safety recommendations of tES in children, reduced current intensities (~1 mA) are often used (Krishnan et al., 2015). In this trial, 0.7mA will be the dose for the intervention group, 20 min duration per session. In the active-tPCS group, there was a 10-second ramp-up to 0.7 mA, maintained for the session, and a 10-second ramp-down at the end. In the sham group, there will be a 10-second ramp-up to 0.7 mA followed immediately by a 10-second ramp-down to zero for the remainder of the session.

### 6.2 Treatment Procedure

Treatment in the current trial will be performed over a one-month period, consisting of the following:

- 6.2.1 One day (approximately 3 hours) of baseline assessment of ATEC, ABC, CSHQ and WISC, performed by qualified occupational therapists and child psychologists, through clinical observation and parent interviews.
- 6.2.2 tPCS: Twenty consecutive sessions of active-tPCS in the intervention group or sham-tPCS in the control group, 20-min per session, once a day, 5 times a week (Monday to Friday), over 4 weeks. tPCS will be administered by a trained therapist or doctor in clinic. The same therapist/ doctor will not take part in patient assessments. The current amplitude will be at 0.7mA for active stimulation in the intervention group, with 10 seconds ramp up at the start and 10 seconds ramp down at the end of the session. For sham stimulation in the control group, there will be an output current for the first 10 seconds and then the stimulation intensity will recede to 0, but the power indicator on the front of the device will continue to light up just like in active stimulation, even after the current is discontinued, to allow for masked stimulation.

tPCS Pre-treatment procedures: Subjects receiving active or sham tPCS treatment will first be fitted with a Velcro head strap that is used to firmly secure the anode and cathode circular silver-fiber cotton electrodes to the scalp according to the trial montage i.e. Cathode on the left dorsolateral pre-frontal cortex (L-dLPFC) and Anode on the right cerebellar hemisphere. The electrodes are thoroughly pre-soaked with 0.9%NaCl solution for 10 mins before application.

tPCS Montage (Electrode Placement): See Figure 3. During both the active and sham tPCS treatment, the Anode electrode will be placed on the right cerebellar hemisphere, 1 cm below and 4 cm to the right of theinion (Red), the Cathode electrode will be placed on the left dorsolateral prefrontal cortex, corresponding to the F3 position of the EEG10-20 electrode placement system (White), located using the Beam-F3 method. The electrodes will be secured to the scalp using the pre-fitted Velcro head strap.

**Figure 3. Electrode placement for tPCS (Active and Sham)**

#### 6.2.3 Concomitant therapy:

After tPCS, participants in both active and sham-tPCS groups will be given standard behavioural therapy over 4 weeks in the study period. There will be a 1-hour therapy session in addition to daily active or sham tPCS. Standard behavioural therapy includes Applied Behaviour Analysis, structured education, play-based therapy and speech therapy. Each of the four therapies will be administered five times per subject, totaling 20 hours therapy per subject. Standard therapy is performed by experienced therapists with at least five-year experience.

#### 6.2.4 One day (approximately 3 hours) of post-treatment assessment of ATEC, ABC and CSHQ, performed by qualified occupational therapists and child psychologists, through clinical observation and parent interviews.

### 6.3 Specific treatment adherence requirements/strategies

In this study, the tPCS intervention will be provided to participants free-of-charge in the eight hospital sites. The participants will not receive any monetary payments or gifts for their participation in the study.

### 6.4 Blinding

The study is double-blinded, both the study subjects (including their parents /caretakers) and outcome evaluators are blinded and will not know about the group allocation. The devices used in the active and sham tPCS groups will be identical, each hospital involved in this study will allocate two separate treatment rooms to place the active-tPCS and sham-tPCS devices. The two rooms will be reasonably separated in different levels of the building so that there will be no chance of communication between the two groups. Participants and accompanying parents/guardians will be asked to return to the same treatment room for all 20 recurring daily treatments. All subjects will be naïve users of tPCS, they will not be aware of the difference between active and sham stimulation condition and will be informed by the treating doctor that the sensation felt is a typical tPCS sensation, effectively blinding subjects to the different treatment conditions. Given that tPCS is non-invasive and effects of tPCS are temporary, there will be no emergency unblinding in this trial. Should SAEs occur, safety handling will follow procedures as stated under Section 7.

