### 1.2.3 Safety of tES in Children

While there are yet no studies done involving tPCS and children with ASD, the safety of tPCS had been

investigated in childhood cerebral palsy and in adult neurological disorders such as Parkinson's disease, chronic visceral pain and disorder of consciousness, with no adverse events recorded. At present, it is generally considered that an output current between 0-2mA, and the single stimulation time is less than 40 minutes is considered relatively safe. There is no exact guidelines for tES dosing in children although a dose of up to 1mA is typically used. Krishnan C et.al conducted a comprehensive statistical analysis of 48 clinical studies involving more than 513 children and / or adolescents with non-invasive brain stimulation. They found that the most common adverse reaction of tES among people under 18 years of age was skin tingling, with an incidence rate of 11.5%, followed by skin itching, with an incidence rate of 5.8%. These adverse reactions were transient and non-persistent. In terms of cognitive adverse events, treatment-emergent mania and hypomania have been reported in unipolar and bipolar depression treatment in tDCS trials in diseased adults. Finally, drug interactions with tDCS have been reported, with antipsychotics with high D2 affinity such as Haloperidol and Risperidone reported to suppress neuromodulation-induced plasticity while benzodiazepines were associated with an increase in depression scores when used in conjunction with tDCS.

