## 7 Safety Measurements

### 7.1 Definitions

An adverse event (AE) is any untoward medical occurrence in a clinical investigation subject who is administered a medicinal product or investigational product, and which does not necessarily have a causal relationship with this treatment. An adverse event (AE) can therefore be any unfavorable and unintended sign (including an abnormal laboratory finding), symptom, or disease temporally associated with the use of a medicinal (investigational) product, whether or not related to the medicinal (investigational) product. A serious adverse event (SAE) is any untoward medical occurrence that at any dose:

- results in death
- is life-threatening
- requires inpatient hospitalization or prolongation of existing hospitalization
- results in persistent or significant disability/incapacity, or
- is a congenital anomaly/birth defect

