### **9.2.3 Safety analysis**

Intervention is non-invasive, potential side effects are only limited to influences upon the skin where the electrodes are placed. Participant discomfort will be closely monitored. Urine test will be conducted before and after the intervention to check for any unintended metabolic changes. Adverse event monitoring will be reported in the full study population and described in a table. Chi-Square test will be used for any comparison of the incidence rate of adverse events between the two groups.

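### Families are told that what is felt is typical of tPCS and then complete the adverse event log, with no stated rule that such sensations are still recorded, so tingling and itching may be under-recorded

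*Combined protocol and SAP*

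**What the plan says.** Section 6.4 (Blinding) opens by counting parents and caretakers among the blinded study subjects. As a blinding measure it then says that subjects "will be informed by the treating doctor that the sensation felt is a typical tPCS sensation". The message is the same in both arms.

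Section 4.3, footnote 6, sets out who records harms: "Parents / caregivers of both groups will be asked to fill out the adverse event log after each session".

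Section 1.2.3 gives the expected harms from a review of non-invasive brain stimulation in children and adolescents: "skin tingling, with an incidence rate of 11.5"%, followed by "skin itching, with an incidence rate of 5.8"%. Section 2.4.1 lists the first of these as a risk of this device: "tPCS may cause discomfort or tingling sensation to some people". It also lists skin redness and headache.

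Section 7.1 defines an adverse event broadly, to include "any unfavorable and unintended sign", whether or not related to the product. It does not say whether an expected sensation counts. Section 9.2.3 plans a descriptive table of adverse events, and adds: "Chi-Square test will be used for any comparison of the incidence rate of adverse events between the two groups".

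**The concern.** Each instruction is reasonable alone. The difficulty is that they meet in the same people and the plan does not say how they fit together. A parent who has heard from the doctor that tingling is what tPCS feels like has some reason to regard it as part of the procedure and not as something untoward to write down.

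The reassurance also falls on the kind of harm that the plan expects, since section 9.2.3 regards side effects as confined to the skin under the electrodes. The sensation is the child's. Children may be as young as 3 or have an IQ only just above 35, and no supplied section says that the child is asked.

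No second route of capture is described in any detail. Section 9.2.3 promises close monitoring of discomfort without saying who does it or how. Section 7.2 keeps related non-serious events at the site, and for safety the monthly committee report in Appendix 5 is specified to summarise serious events.

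At stake is the safety description of a treatment that section 1.2.3 says has not been studied in children with ASD. Stated rates could be too low, and a comparison showing no difference could partly reflect what was written down.

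**Working it through.** The plan gives no figure for the adverse event comparison, so there is none to reproduce. The calculation below shows how logging loss would act. It does not estimate the loss.

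**Inputs from the documents**
- 170 children per arm (section 4.2).
- Two-sided tests at 0.05 (section 9.2.1).
- Tingling 11.5% on active, taking the section 1.2.3 figure for tES in general.

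**Assumptions (no figure in the documents)**
- True tingling on sham: 3%, with a range of 2% to 5%. Some is plausible because sham also delivers current briefly (sections 4.3 and 6.1).
- Share of affected children who are logged: 100%, 50% or 25%.

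**Formulas**
- Logged rate in an arm = true rate × share logged.
- Power = Φ[(d − 1.96 × SE0) / SE1], where d is the difference in logged rates, SE0 = √[2p̄(1 − p̄)/170] with p̄ the mean of the two rates, and SE1 = √[(p1(1 − p1) + p2(1 − p2))/170].

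**Full logging, 11.5% v 3%.** d = 0.085, p̄ = 0.0725, SE0 = 0.02813, SE1 = 0.02775. (0.085 − 1.96 × 0.02813)/0.02775 = 1.08, so power is 86%. Expected active cases: 170 × 0.115 = 19.6.

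**Half logged in both arms, 5.75% v 1.5%.** d = 0.0425, p̄ = 0.03625, SE0 = 0.02027, SE1 = 0.02014. (0.0425 − 1.96 × 0.02027)/0.02014 = 0.14, so power is 55%. Expected active cases: 9.8.

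| Share logged (both arms) | Active v sham | Risk difference | Risk ratio | Power |
|---|---|---|---|---|
| 100% | 11.5% v 3% | 8.5 points | 3.83 | 86% |
| 50% | 5.75% v 1.5% | 4.25 points | 3.83 | 55% |
| 25% | 2.9% v 0.75% | 2.1 points | 3.83 | 31% |

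With sham at 2%, power goes from 94% at full logging to 68% at half. With sham at 5%, it goes from 59% to 32%. The risk ratio is unchanged by equal loss, because the share logged cancels.

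**Unequal logging, sham 3%**
- 25% logged on active, 50% on sham: 2.875% v 1.5%. The difference is 1.4 points and the ratio 1.92, both below the full-logging values.
- 50% on active, 25% on sham: 5.75% v 0.75%. The difference is 5.0 points and the ratio 7.67, so the ratio moves away from the null.
- 100% on active, 50% on sham: 11.5% v 1.5%. The difference is 10.0 points, larger than the true 8.5.

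The direction therefore depends on which families log less.

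**Effect of repeated logging.** The log is completed after each of 20 sessions. If incidence is counted per child, one entry is enough. A child with tingling in 5 sessions, each logged with an independent 25% chance, has at least one entry with probability 1 − 0.75^5 = 76%. Independence is favourable to the plan: a family that has accepted tingling as normal may omit it every time.

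**The case against.** A reader might infer that tingling will be left off the log and that the arm comparison is therefore biased towards no difference. The documents do not support that.

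- No section exempts expected sensations. Section 7.3 says that all adverse events of tPCS in all participants are logged, section 7.4 sends any complaint to the investigators immediately, and section 9.2.3 says that discomfort is monitored. Calling a sensation typical is not an instruction to leave it out.
- The log form is not supplied and the consent pages were removed, so prompts or advice to report tingling may exist there. Section 8.2 and the contents list name only the ATEC, ABC and CSHQ data forms. That leaves the content of the log unspecified but does not show that it lacks prompts.
- The message is the same in both arms, and equal loss leaves the risk ratio alone.
- The 11.5% is for tES in general. Section 1.2.3 reports no adverse events in the tPCS studies that it cites, and it calls the skin reactions transient.
- The adverse event comparison is not a powered hypothesis, and efficacy results are untouched.

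All of this stands against any claim of certainty or fixed direction. It does not supply the missing rule. A general statement that all adverse events are logged does not tell a parent whether a sensation that the doctor has called typical is one, and consent wording listing tingling as a risk would not by itself make the log ask about it.

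**Conclusion.** The point holds as a risk of under-recording. Two stated instructions meet in the same families, and no supplied text says that a sensation called typical is still recorded or asked about by name. Any under-recording would understate absolute tingling and itching rates. If the loss is similar in both arms, it would also reduce the risk difference and the power of the chi-square test, but not the risk ratio. If logging differs by arm, the direction is open.

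The size cannot be derived from the documents. The fall in power from 86% to 55% rests on applying the general tES rate to this device, an assumed 3% on sham and an assumed half of affected children logged equally in both arms. Repeated entries over 20 sessions would recover part of that loss. This is an inexpensive improvement in capturing harms. It does not show that the planned comparison is biased.

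**What to change.** Leave the blinding statement in section 6.4 unchanged.

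- **Section 4.3, footnote 6:** have the existing post-session log ask families in both arms the same fixed yes/no questions on tingling, itching, skin redness, discomfort and headache. Add a line on the form that these are recorded even if they have been described as typical.
- **Section 9.2.3:** report the proportion of children with each solicited item by arm, with the risk difference and 95% confidence interval, separately from spontaneously reported adverse events.

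The cost is one form revision and a short addition to section 9.2.3, with no new visits or staff. The downside is that prompting will make reported rates of mild events look somewhat higher in both arms. Presenting solicited and spontaneous reports separately lets readers see this.
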